# Usefulness of Respiratory Stability Time-Guided Management to Prevent Readmission of Chronic Heart Failure Patients at Home: A Multicenter, Single-Arm, Open-Label Clinical Study (ITMETHOD-HF-III)

**DOI:** 10.3390/jcm14134653

**Published:** 2025-07-01

**Keywords:** telemonitoring, congestion, heart failure, hemodynamics

## Abstract

**Background**: Telemonitoring aimed at detecting subclinical heart failure and facilitating medication up-titration offers a promising approach to reducing heart failure hospitalizations. Our team has recently developed a non-invasive metric called “respiratory stability time (RST)”, which quantifies respiratory instability, a surrogate marker of subclinical worsening heart failure. A decrease in RST below 20 s predicts the onset of worsening heart failure within 28 days. However, the clinical utility of RST-guided management in reducing mortality and heart failure hospitalizations remains uncertain. **Methods**: The Innovative Tele-Monitoring Environment To Halt Ongoing Deterioration of Heart Failure-III (ITMETHOD-HF-III) is a non-blinded, interventional, multicenter, single-arm study. Eighty heart failure patients with a history of at least two prior hospitalizations for heart failure will be enrolled. After validating the robustness of RST measurements, participants will be monitored for 1.5 years through daily RST measurements. Mandatory up-titration of heart failure medications will be started if RST values decrease below 20 s for two consecutive days or decrease progressively below 30 s over 10–90 days from RST values above 45 s maintained for over 1 month, irrespective of the presence of heart failure signs/symptoms. Medication adjustment will continue until RST exceeds 30 s. The study will compare a composite endpoint of heart failure hospitalization and cardiac death between the present RST-guided group and a historical control group from the ITMETHOD-HF-II trial, in which management was based on patients’ symptoms. **Results:** We anticipate that the precent ITMETHOD-HF-III study will demonstrate that mandatory, RST-guided heart failure management significantly reduces the incidence of the primary composite endpoint—heart failure hospitalization and cardiac death—compared with symptom-guided standard care in the historical control group (ITMETHOD-HF-II). **Conclusions**: The ITMETHOD-HF-III study aims to demonstrate the clinical efficacy of RST-guided management in reducing heart failure hospitalization rates and cardiac mortality by enabling early detection of subclinical heart failure and facilitating timely medication adjustments, irrespective of heart failure signs/symptoms. If successful, RST-guided management could establish a new standard for telemonitoring heart failure patients in outpatient settings.

## 1. Introduction

Despite the widespread adoption of established pharmacological treatments for heart failure, the morbidity and mortality rates of heart failure patients remain unacceptably high [1]. Notably, readmission due to worsening heart failure is a strong predictor of subsequent hospitalizations and increased mortality [2]. Recurrent hospitalizations are not only associated with adverse clinical outcomes, but they also contribute to a diminished quality of life and increased healthcare costs. Thus, preventing heart failure-related hospitalizations is a critical strategy in mitigating the global burden of this condition [3].

A major challenge in reducing hospitalizations lies in the early identification of worsening heart failure to enable timely optimization of medical therapy [4]. Typically, patients seek medical attention at outpatient clinics when they experience symptoms of heart failure, such as dyspnea on exertion [5]. Clinicians then evaluate heart failure severity using physical examinations, chest radiography, and plasma B-type natriuretic peptide measurements. However, the heart failure often progresses insidiously, preceding the onset of overt symptoms [6]. Consequently, by the time symptoms become evident, the condition has frequently advanced to a stage where hospitalization is unavoidable [7].

Telemonitoring has attracted significant attention as a promising tool for tracking heart failure progression and detecting early signs of heart failure deterioration before symptom onset [8]. Conventional parameters such as blood pressure, heart rate, respiratory rate, and body weight are easily measurable without specialized equipment but lack disease specificity, limiting their utility in early detection of heart failure exacerbations [9].

Several advanced modalities have been proposed to enhance telemonitoring capabilities. Thoracic impedance monitoring, for example, has been used in patients with cardiac resynchronization therapy devices [10]. However, its application is restricted to individuals with implantable cardiac devices, and its high false-positive rate necessitates concurrent evaluation of additional variables for accurate assessment [11].

Another notable innovation is the CardioMEMS system, which involves implanting a sensor in the pulmonary artery to continuously monitor pulmonary artery pressure [12]. In the CHAMPION trial, CardioMEMS-guided therapy significantly reduced heart failure hospitalizations by enabling earlier intervention based on pulmonary artery pressure trajectory, rather than relying solely on clinical symptoms or weight changes [13]. However, the invasive nature of sensor implantation and the associated high costs pose significant barriers to widespread adoption, particularly in regions where the device is not yet available, such as Japan [14].

Recently, our team introduced a novel, non-invasive metric termed “**Respiratory Stability Time (RST)**”, which quantifies respiratory instability (Figure 1) [15]. Respiratory instability, such as Cheyne–Stokes respiration or irregular rapid shallow breathing without periodicity, reflects underlying neuro-hormonal, hemodynamic, and respiratory derangements associated with worsening heart failure. Using a proprietary algorithm, we developed an automated system to calculate RST.

Previous studies have demonstrated that patients with RST values below 20 s exhibit significantly worse 1-year clinical outcomes than those with higher RST values [15]. The IMIZUNO-HOME trial, which incorporated telemonitoring of multiple parameters, including RST, showed that RST independently predicted the onset of heart failure exacerbations [16]. During index hospitalizations due to heart failure, RST improvements correlated with the resolution of heart failure-related congestion [17]. In another study, therapeutic interventions such as transcatheter aortic valve replacement for severe aortic stenosis were shown to ameliorate RST levels [18].

**Figure 1 jcm-14-04653-f001:**
[figure not shown]
Methodology to calculate RST values (reused with permission) [18]. All spectral power is normalized by the power spectral density or the ratio of the maximum power of the components. All respiration frequency points with a power spectral density > 10% are equally adopted in the assessment of respiratory instability. Very low-frequency points of the periodic breathing curve are only adopted if the power spectral density of the very low-frequency component is >50% of the maximum power of the respiratory component. Respiratory frequency points are evaluated using standard deviation, and RST value is defined as the inverse of the standard deviation. CSR, Cheyne–Stokes respiration; Resp, respiration; RST, respiratory stability time.

Building on these findings, a multicenter, prospective study, **Innovative Tele-Monitoring Environment To Halt Ongoing Deterioration of Heart Failure-I (ITMETHOD-HF-I)**, was conducted from 2017 to 2019 [19]. This study used an upgraded RST monitoring system and identified an RST threshold of 20 s as the optimal cut-off for predicting future heart failure-related hospitalizations.

Subsequently, the **ITMETHOD-HF-II trial**, a multicenter, prospective, randomized, controlled study, evaluated the clinical utility of prospective RST monitoring. Patients were advised to visit outpatient clinics if their RST fell below 20 s, although the decision to adjust medications was left to the discretion of the attending physicians. Clinical decisions eventually relied on traditional signs and symptoms assessed during outpatient visits despite continuous RST monitoring.

To fully elucidate the clinical implications of RST-guided management, particularly its potential to detect “occult” heart failure progression before symptom onset, give us a chance to enhance heart failure medications, and prevent worsening heart failure, therapeutic intervention must be systematically aligned with RST alerts “alone”, irrespective of heart failure signs/symptoms. The current **ITMETHOD-HF-III study** addresses this gap by “mandating” the up-titration of heart failure medications whenever RST reaches the alert threshold, irrespective of clinical signs or symptoms. This single-arm, multicenter, prospective study will compare outcomes, including heart failure hospitalizations and cardiac mortality, against those observed in ITMETHOD-HF II, where medication adjustments were discretionary.

## 2. Materials and Methods

### 2.1. Patient Selection

Patients who fulfill all inclusion criteria and meet none of the exclusion criteria will be eligible for enrollment in this study (Table 1). Participants from the previous ITMETHOD-HF-II trial will also be included as a historical control group for comparative analysis. The patient selection process will follow a two-step registration system, as illustrated in Figure 2.

(1)Primary registration

Patients with chronic heart failure and a history of at least two prior hospitalizations for heart failure will qualify for primary registration. However, individuals with conditions that may affect RST measurements, including a history of stroke, the use of mechanical circulatory support devices, or a diagnosis of obstructive sleep apnea syndrome, will be excluded at this stage.

(2)Secondary registration

Patients listed in the primary registration will undergo RST measurement trials. Only those whose RST can be measured accurately will advance to secondary registration. Upon inclusion in the secondary registration, these patients will begin RST-guided telemonitoring.

### 2.2. Study Design

After obtaining informed consent, patients will undergo a screening process to determine their eligibility (Figure 2). Eligible patients will be enrolled in the primary registration phase, during which the telemonitoring system will be set up, and initial RST measurements will be conducted. Upon verification of accurate RST measurements, patients will progress to secondary registration. At this stage, RST-guided management will start.

Clinical parameters, including RST values, will be continuously monitored over a 1.5-year observation period. The historical control group will consist of participants from the prior **ITMETHOD-HF II trial**, in which RST values were monitored, but therapeutic decisions were left to the discretion of attending physicians. In contrast, the current study “mandates” therapeutic interventions whenever RST values fall below the alert threshold, irrespective of clinical signs or symptoms.

### 2.3. RST Measurement

The telemonitoring system used in this study comprises a piezoelectric, non-contact sensor (Nemuri SCAN, Paramount Bed Co., Ltd., Tokyo, Japan) positioned beneath the bed sheet, connected to a microcomputer that serves as an Internet-enabled gateway installed in the patient’s home (Figure 3) [19]. This system continuously collects respiratory signals and monitors the patient’s time spent lying in bed.

During the study period, respiratory signals are captured nightly at a sampling frequency of 16 Hz, spanning the entire duration of the patient’s sleep. These signals are transmitted to a cloud server, where all-night RST values are calculated and stored (Figure 3) [15]. To standardize the analysis, data collected during the fixed hours of 23:00 to 5:00 are used. All respiratory signals transmitted to the cloud are automatically processed and analyzed using an RST calculation program (HeartLab, Inc., Kobe, Japan) by 8:30 am every morning.

The detailed methodology for RST measurement has been previously described [15]. As part of the pre-processing pipeline (Figure 4), the direct current component of the signals is removed to eliminate zero-frequency impulses, and a zero-phase digital filter is applied to isolate respiratory signals by excluding high-frequency components above 0.5 Hz. Subsequently, the processed signals are resampled at 4 Hz. To estimate RST, two frequency ranges are analyzed as previously established.

(1)
**Respiratory frequency components**

These are derived from instantaneous respiratory signals after the exclusion of high- and low-frequency noise using a 5th-order bandpass Butterworth filter with cut-off frequencies of 0.11 Hz and 0.5 Hz.

(2)
**Very low-frequency components**

These correspond to periodic breathing patterns and are obtained by tracing the peaks of instantaneous respiratory signals, adjusting the baseline to zero, and applying a bandpass filter with cut-off frequencies of 0.008 Hz and 0.04 Hz.

For serial analysis of all-night RST, respiratory signals are divided into consecutive 5 min segments, updated every 50 s. A minimum of 420 segments (≥350 min) of data are required for analysis each night. For each segment, the **maximum entropy method** is applied to extract specific respiratory and periodic breathing components from the spectral data.

Spectral power is normalized as a percentage of the maximum respiratory power. Respiratory frequency points with spectral power exceeding 10% of the maximum respiratory power are considered in the evaluation of respiratory instability. For periodic breathing components, only very low-frequency points with maximum power exceeding 50% of the respiratory components’ maximum power are included in the RST calculation.

For each epoch, the standard deviation of the respiratory frequency distribution is calculated, and RST is defined as the reciprocal of this standard deviation. All-night RST values are then averaged to provide a single representative measure of nightly respiratory instability.

RST values are updated daily, and a 3-day moving average is calculated to monitor trends. These trends are visualized on the monitoring center’s dashboard, where representative high and low RST values are displayed (Figure 5A,B).

### 2.4. RST-Guided Management

Therapeutic intervention is initiated by up-titrating heart failure medications when daily RST meets either of the following alert thresholds for two consecutive days, irrespective of the presence of heart failure symptoms: (1) the RST value falls below 20 s for two consecutive days; or (2) the average RST value remains above 45 s for over one month but then decreases progressively to below 30 s within a period of 10 to 90 days. A visual decision tree outlining the RST alert criteria and subsequent actions is summarized in Figure 6.

Patients are instructed to visit the outpatient clinic within three business days when their RST reaches the alert threshold. If, despite therapeutic intervention, the RST does not improve to exceed 30 s, patients will be asked to revisit the outpatient clinic for further evaluation and intensification of treatment. This process will be repeated as necessary until the RST stabilizes above 30 s. Management will continue to ensure sustained improvement in RST levels.

### 2.5. Study Visits and Follow-Up

Following informed consent and initial screening, patients are enrolled in the primary registration. During screening, data are collected on heart failure symptoms, vital signs, chest X-ray, electrocardiogram, laboratory parameters (plasma B-type natriuretic peptide or serum NT-pro B-type natriuretic peptide, hemoglobin, serum creatinine, and blood urea nitrogen), transthoracic echocardiography, and medication history (Table 2). On confirmation of appropriate RST measurement, patients are included in the secondary registration, and RST-guided management is started.

Throughout the 1.5-year observation period, patients are monitored at the outpatient clinic at regular intervals, typically once per month. Clinical data collected at each visit are recorded when available. In the event of hospitalization due to low RST, chest X-ray and laboratory tests are mandatory, and the dosage of heart failure medications is systematically up-titrated, regardless of the presence of heart failure symptoms.

### 2.6. Primary and Secondary Outcomes

The primary outcome is defined as a composite of heart failure hospitalization and cardiac death. Heart failure hospitalization is characterized by an admission due to worsening heart failure requiring significant up-titration of diuretic dosage, intravenous diuretic administration, or mechanical circulatory support, with a minimum of 24 h of in-hospital observation.

The secondary outcomes include feasibility, efficacy, and exploratory outcomes. The feasibility of RST telemonitoring is assessed. Efficacy outcomes encompass recurrent heart failure hospitalization, cardiac death, the occurrence of heart failure hospitalization or cardiac death within 60 days following RST decrease, heart failure hospitalization or cardiac death in patients with RST improvement (versus no improvement), heart failure hospitalization or cardiac death in patients with RST decrease (versus no decrease), and the increase of RST within one month following RST decrease. As an exploratory outcome, heart failure hospitalization or cardiac death in patients without RST decrease is also evaluated. All events will be evaluated by the independent committee.

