### 4.3. How to Demonstrate the Clinical Implication of RST-Guided Management

Evidence from previous studies suggests that a decrease in RST below 20 s can predict heart failure hospitalization up to 28 days in advance [19]. However, the clinical efficacy of aggressive therapeutic interventions to prevent such hospitalizations in real-world daily practice remains uncertain.

In the ITMETHOD-HF-II trial, patients were encouraged to be admitted when their RST fell below 20 s. However, therapeutic decisions, including the up-titration of heart failure medications, were left to the discretion of attending physicians. In many cases, medications were not adjusted, likely because patients were asymptomatic due to early hospital admission. To unequivocally demonstrate the utility of RST in identifying subclinical heart failure and preventing hospitalizations, “mandatory” up-titration of heart failure medications is essential when RST values fall below this threshold.

Findings from the ITMETHOD-HF-II study reinforce this approach. All patients who achieved RST values of ≥30 s within 14 days by therapeutic intervention successfully avoided heart failure hospitalizations. This is a rationale why we set 30 s of RST as a therapeutic target. Based on these findings, we strongly propose repeating therapeutic adjustments until RST values exceed 30 s.

However, mandatory interventions carry potential risks, particularly in patients with hypovolemia or renal impairment, in whom hemodynamic instability may occur. Therefore, careful risk-benefit analyses are crucial to ensure the safety of mandatory interventions, especially in asymptomatic patients.

It is also important to recognize that not all participants may experience an increase in RST despite aggressive therapeutic interventions. A thorough assessment of patient characteristics, the types of interventions attempted, and clinical outcomes is necessary to identify refractory cohorts. These findings will help inform the development of tailored therapeutic strategies for these populations in future studies.

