### 4.4. Study Limitation

This study protocol has several limitations that warrant consideration. First, the ITMETHOD-HF-III study is designed as a single-arm, non-randomized trial utilizing a historical control group from the previous ITMETHOD-HF-II study. Although this approach facilitates rapid implementation and comparative analysis, it inherently limits the ability to control for unmeasured confounders and time-dependent biases such as changes in clinical practice, therapy use, and healthcare delivery. Differences in clinical practices, patient management strategies, or healthcare delivery systems between the two study periods may influence outcomes independently of the intervention itself. We may add propensity score analysis to further address residual confounding.

Second, the protocol mandates therapeutic up-titration solely based on RST values, irrespective of heart failure symptoms or physical findings. While this strategy aims to validate the utility of RST in detecting subclinical deterioration, it also introduces a potential risk of overtreatment, particularly in patients with borderline RST values or comorbidities such as renal dysfunction or hypovolemia. Final decision to strengthen the therapy, including the up-titration of diuretic dose, is at the discretion of the attending physicians. The response of RST values to each therapeutic intervention also remains a concern to be analyzed. The safety and tolerability of such aggressive, symptom-independent interventions remain to be fully established.

Third, RST measurement relies on a piezoelectric sensor and proprietary algorithm, which, although validated in previous studies, may be influenced by factors such as sleep position, body movement, and comorbid pulmonary or neurological conditions. We defined several stringent inclusion and exclusion criteria to mitigate these confounders. Conversely, such strict criteria may limit generalizability to real-world clinical management. Further studies are warranted to evaluate the applicability of this system and our therapeutic strategy utilizing this technology.

Fourth, due to the open-label, single-arm design, neither participants nor clinicians are blinded to the intervention, which may introduce bias in outcome ascertainment and therapeutic decision-making. Although outcome adjudication is performed in a blinded manner by an independent committee, the potential for performance and detection bias cannot be fully excluded.

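### The heart failure hospitalization endpoint does not separate an admission prompted only by low RST from true decompensation, so a difference in alert handling between the two cohorts can bias the comparison in either direction

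*Protocol article*

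**What the plan says.** **Endpoint.** Section 2.6 defines heart failure hospitalization as "an admission due to worsening heart failure requiring significant up-titration of diuretic dosage, intravenous diuretic administration, or mechanical circulatory support". The stay must last at least 24 h. Intravenous diuretics are one of three alternatives, so a significant increase in diuretic dose is enough. An independent committee evaluates all events; section 4.4 adds that it is blinded.

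**New cohort.** Section 2.4 makes the alert response an outpatient visit: "Patients are instructed to visit the outpatient clinic within three business days when their RST reaches the alert threshold". The Figure 6 legend agrees. Section 2.5 describes something else: "In the event of hospitalization due to low RST, chest X-ray and laboratory tests are mandatory", and then "the dosage of heart failure medications is systematically up-titrated, regardless of the presence of heart failure symptoms". Section 4.4 says: "Final decision to strengthen the therapy, including the up-titration of diuretic dose, is at the discretion of the attending physicians".

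**Historical control (ITMETHOD-HF-II).** The Introduction, after Figure 1, says: "Patients were advised to visit outpatient clinics if their RST fell below 20 s". Section 4.3 says: "In the ITMETHOD-HF-II trial, patients were encouraged to be admitted when their RST fell below 20 s". Sections 1, 2.2 and 4.3 agree that treatment changes were at the physician's discretion, and section 4.3 adds that often none were made.

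**Planning figures.** Section 2.7 gives 52 controls, a 1.5-year heart failure admission rate of 43.1%, an assumed 21.6% in the new cohort, and 80 patients to be enrolled.

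**The concern.** An endpoint should be something the intervention may prevent, not something the intervention pathway can itself generate. Here a low RST is the trigger for treatment, the abstract describes low RST as a surrogate marker of subclinical worsening heart failure, and up-titration of medication is both the study treatment and, for diuretics, part of the event definition. If a patient is admitted because of an alert and diuretics are significantly raised, the definition does not say whether that is an event.

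This matters more than it would in a randomised trial. The two cohorts come from different studies, and the alert pathway may have differed between them. If control patients really were brought into hospital on an alert and new patients attend clinic instead, admissions can fall with no clinical benefit. If new patients are admitted on an alert with treatment driven by the protocol, events are added to the new cohort and a real benefit is diluted. Adjusting for baseline covariates, as section 2.8 plans, cannot repair a difference in what is counted.

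**Working it through.** **1. Can an alert-only admission meet each part of the definition?**

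| Criterion in 2.6 | New cohort | Historical control |
|---|---|---|
| Admission of at least 24 h | Foreseen in 2.5; 2.4 and Figure 6 say clinic visit | 4.3 says admission encouraged; Introduction says clinic visit |
| Due to worsening heart failure | Open: depends on whether low RST alone is read as worsening | Open, same reason |
| Significant diuretic up-titration (or IV diuretic, or mechanical support) | Possible: 2.5 calls for up-titration of heart failure drugs, and 4.4 shows diuretics are among them but leaves the final decision to the physician | Possible only where the physician chose to intensify diuretics |

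So the overlap is possible in both cohorts and automatic in neither. The study protocol drives it only in the new one.

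**2. Planning figures.** Half of 43.1% is 21.55%, which matches the stated 21.6%. Under exponential event times, HR = ln(1 − p_new) / ln(1 − p_control) = ln(0.784) / ln(0.569) = −0.2433 / −0.5639 = 0.43. Expected control events: 0.431 × 52 = 22.4, about 22. The documents give no number of alert-prompted admissions, so all counts below are assumptions.

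**3. Alert-only events in the control, no true benefit.** The new cohort then has the control rate without those k events: HR = ln(1 − (0.431 − k/52)) / ln(0.569).

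| k of about 22 | Rate without them | Apparent HR |
|---|---|---|
| 3 | 0.373 | −0.4673 / −0.5639 = 0.83 |
| 5 | 0.335 | −0.4077 / −0.5639 = 0.72 |
| 8 | 0.277 | −0.3246 / −0.5639 = 0.58 |

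This assumes that none of the k patients would later have had a true event. If half would have (k/2 in place of k), the values are 0.91, 0.86 and 0.78.

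**4. Alert-only events added in the new cohort, planned benefit true.** HR = ln(1 − (0.216 + k/80)) / ln(0.569). Power is from the Schoenfeld formula, Φ(|ln HR| × √(D × a(1 − a)) − 1.96), with D the expected events in 52 controls and 80 new patients and a = 52/132.

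| k of 80 | Observed rate | D | HR | Power |
|---|---|---|---|---|
| 0 | 0.216 | 39.7 | 0.43 | 73% |
| 3 | 0.254 | 42.7 | 0.52 | 56% |
| 5 | 0.279 | 44.7 | 0.58 | 43% |
| 8 | 0.316 | 47.7 | 0.67 | 27% |

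This assumes no overlap with the true events in the 21.6%. The printed power of 25% in section 2.7 is a separate matter and is not used here.

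**5. Both cohorts affected.** If the same share of otherwise event-free patients (5%, 10% or 20%) is counted in both cohorts, the planned HR of 0.43 becomes 0.48, 0.52 or 0.59. Equal contamination pulls the result towards 1; unequal contamination can move it either way.

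**The case against.** The other side has substantial points.

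- A reader might infer that every alert-prompted admission becomes an event because the protocol was followed. The text does not support that. The admission must be due to worsening heart failure and must require a significant diuretic increase, while section 2.5 speaks of heart failure drugs in general and section 4.4 leaves the final decision to the physician.
- A reader might also infer that protocol-driven up-titration operates in both cohorts. It does not: in ITMETHOD-HF-II treatment was discretionary and often unchanged, and an admission without intensified treatment does not meet the definition.
- Table 2 has separate columns for the examination at an RST decrease and for an exacerbation, and requires a judgement on inpatient care at the former. Admission is thus a further decision. The word hospitalization in section 2.5 may be loose wording for a hospital visit.
- Section 4.3 reports that all ITMETHOD-HF-II patients who reached an RST of at least 30 s within 14 days by intervention avoided heart failure hospitalization. That would be hard to reconcile with routine counting of treated alert admissions as events.
- A blinded independent committee evaluates events, and its detailed criteria may sit in the full protocol or a charter.

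These points limit the claim to a possibility and leave its frequency unknown. They do not remove it. The 14-day finding covers only patients who responded. The decision on inpatient care at an alert is made by unblinded clinicians. Blinded adjudication helps only once the definition says which class an RST-only admission belongs to, and the stated definition is silent. If section 2.5 or 4.3 is loosely worded, the sponsor alone can say so.

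**Conclusion.** The point holds as a conditional risk in a stated definition. The endpoint as worded does not distinguish an admission prompted by low RST alone from decompensation, and the document contradicts itself on whether alerts led to a clinic visit or an admission, in the control and in the new cohort.

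It would go too far to say that the comparison is biased, or biased in favour of the intervention. Extra events in the control favour the intervention; extra events in the new cohort count against it; the net direction cannot be determined from the document. The hazard ratios above rest on assumed counts, one cohort affected at a time, exponential event times and no overlap with true events. They show only that, with about 22 control events, a handful of differently classified admissions could change the result.

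**What to change.** 1. In section 2.6, state that an admission counts only if the blinded committee, with RST data masked, confirms worsening heart failure on evidence other than RST: symptoms or signs, or chest X-ray or BNP where available. Classify admissions prompted by low RST alone as a separate category.
2. Apply the same rule to all ITMETHOD-HF-II control admissions from the records available, and restate the control rate if it changes.
3. Add a sensitivity analysis that counts RST-only admissions as events in both cohorts.
4. Reconcile the Introduction with section 4.3 on what control patients were told to do, and sections 2.4 and 2.5 and Figure 6 on what follows an alert in the new cohort. This asks for consistency, not for a particular pathway.

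Cost: revised endpoint wording, a reason-for-admission field, and re-review of about 22 or more control admissions. X-ray or BNP may be missing for some control admissions, which is why the rule also accepts symptoms or signs. The control rate may become less favourable to the planned comparison. Data collection in the new cohort otherwise changes little, because Table 2 already requires symptoms, examination findings, and chest X-ray or BNP at an RST-decrease visit and at an exacerbation.
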